## Abstract

Background/Objectives: This protocol describes a study to investigate the feasibility and preliminary efficacy of a novel Teaching Kitchen Multisite Trial (TK-MT) for adults with cardiometabolic abnormalities. The TK-MT protocol describes a hybrid lifestyle intervention combining in-person and virtual instruction in culinary skills, nutrition education, movement, and mindfulness with community support and behavior change strategies. This 18-month-long randomized controlled trial aims to evaluate the feasibility of implementing a 12-month, 24 class program, assess preliminary study efficacy, and identify barriers and facilitators to implementation. Methods: The intervention program includes 16 weeks of intensive hands-on culinary and lifestyle education classes followed by eight monthly virtual classes. Psychometric assessments and biometric data will be collected at baseline, 4, 12, and 18 months. Semi-structured interviews and open-ended surveys will be conducted during the 12-month follow-up assessment. Results: Feasibility will be assessed through recruitment, attendance, and fidelity data. Secondary outcomes will analyze changes in health behaviors, biometric data, and anthropometric measures using mixed-effects regression models. Qualitative data will undergo thematic analysis. Conclusions: As envisioned and described in detail in this manuscript, this study will inform the development and implementation of reproducible, scalable teaching kitchen interventions. The protocol described here is intended to set the stage for future investigations to evaluate evidence for the impact of teaching kitchen interventions on dietary habits, physical activity, and overall health and well-being.

## 1. Introduction

The White House Challenge to End Hunger and Build Healthy Communities [1,2] brings attention to the critical need for increasing and promoting Food Is Medicine (FIM) [3,4,5] interventions that are aimed at impacting how people eat to improve their health. FIM interventions focus on nutrition security to improve the dimensions of food security and mitigate cardiometabolic risks [4,6]. Culinary medicine is an emerging field within FIM that connects culinary arts to the medical and nutrition sciences to promote healthy dietary behaviors while empowering individuals and communities to take an active role in managing their health through food [5,7,8,9]. Culinary medicine interventions typically involve interactive cooking and nutrition education sessions that aim to improve participants’ cooking knowledge, skills, and confidence to enable sustainable and healthy lifestyle changes [7,8,10].

Previous studies have shown the efficacy of culinary medicine interventions in increasing knowledge of healthy food choices, expanding food budgets, improving food preparation self-efficacy, and enhancing healthy dietary behaviors [11,12,13,14,15,16,17]. Culinary medicine interventions teach practical knowledge and techniques related to basic nutrition, recipe modification, meal planning, knife skills, food preparation, and food storage to help make healthy eating more accessible and attainable [7,8,18]. The interactive format of culinary medicine interventions fosters engagement and empowers participants to translate knowledge learned in classes into actions applied at home [7].

There is limited evidence of the long-term causal impact of culinary medicine interventions participation on clinical outcomes such as body weight, glycemic control, and lipid profiles [11]. While some studies have shown positive associations [14,15,16,19], more robust research designs, particularly randomized controlled trials (RCTs), are needed to establish a causal link between culinary medicine interventions and sustained improvements in clinical health outcomes, both as an independent modality and in conjunction with other medical therapies. Also, there is a need for more CMIs that provide culinary education to participants in their home kitchens so that class components can be learned and practiced in real-world home environments where resources, equipment, and time may be limited. Furthermore, additional studies are needed to better understand how culinary medicine interventions can be tailored to mitigate and eliminate barriers to healthy home cooking such as food accessibility, affordability, and availability.

Teaching kitchen interventions (TKIs) are a subset of culinary medicine interventions that have been described in the literature as “learning laboratories” that seek to promote overall well-being through sustained behavior changes [20]. TKIs teach hands-on culinary and lifestyle skills to participants in physical or virtual teaching kitchens [20]. TKIs are different than other lifestyle programs that address multiple lifestyle pillars such as the Diabetes Prevention Program [21] because TKIs include both didactic and experiential culinary education in addition to lifestyle changes. This broader approach acknowledges the interconnectedness of various lifestyle factors in chronic disease prevention [20]. TKIs emphasize the need to learn (a) basic nutrition information, i.e., what to eat more of, less of, and why; (b) how to shop for and prepare healthy, delicious, easy-to-make, and affordable meals at home; (c) the importance of movement, exercise, rest, and sleep; (d) the relevance and importance of mindfulness as applied to nutrition and life; and (e) how to incorporate evidence-based behavior change strategies into everyday decisions [20,22].

The majority of culinary medicine interventions reported in the literature do not address the additional lifestyle components that are included in TKIs [23]. Movement [24,25,26], mindfulness [27,28,29,30], and behavior change [31,32,33,34,35,36] interventions have been individually evaluated and shown to positively impact risk factors of chronic disease. There is emerging evidence on the compound or multi-modal effect of implementing interventions that provide culinary medicine education alongside some lifestyle components on short-term and long-term behavioral and metabolic risk factors of chronic disease [11,37,38,39]. In addition, previous studies have identified unhealthy dietary behaviors, sedentary lifestyles, and poor sleep hygiene as modifiable risk factors for chronic disease [40]. This TKI is unique in that it (1) has been co-created by numerous clinical and academic institutions that use TKs, (2) provides culinary medicine education, creates a community support system, and mitigates lifestyle risk factors that may have a greater impact on health outcomes than traditional culinary medicine interventions that only focus on cooking and nutrition education or incorporate only some lifestyle education skills, and (3) is being tested across four sites with different populations across the U.S.

This proposed study is the first Teaching Kitchen Multisite RCT (TK-MT) to implement a robust hybrid culinary medicine and lifestyle intervention over an extended study and follow-up period in four diverse U.S. locations. The specific aims of the study described herein will be to evaluate the feasibility, preliminary efficacy, and implementation of the TK-MT for adults with cardiometabolic abnormalities in diverse settings. As envisioned, the findings from this proposed study will inform the development and implementation of a subsequent, larger TKI.

## 2. Materials and Methods

### 2.1. Study Design

The TK-MT will be an 18-month RCT that provides a hybrid teaching kitchen curriculum along with grocery provision to intervention group participants. The teaching kitchen curriculum that will be used for this proposed study was developed and piloted in previous studies [1,2]. The study objectives are to assess feasibility, preliminary efficacy, and the barriers and facilitators of implementing the TK-MT in adults at risk for cardiometabolic disease.

This Teaching Kitchen Multisite Trial (TK-MT) protocol follows the Standard Protocol Items: Recommendations for Interventional Trials (SPIRIT) [41], and this study is registered on clinicaltrials.gov (NCT05628649). This study has been approved by the institutional review board (IRB) for all study sites; Harvard School of Public Health (HSPH) is the IRB of record. Data usage agreements have been created between HSPH and the four study sites. All participants will be provided with an information sheet detailing the study procedures, potential risks, and benefits. Electronic signatures will be collected for informed consent.

### 2.2. Study Setting

Eligible study sites will have a functioning teaching kitchen [42] with facilities that can accommodate up to 30 participants for hands-on cooking activities. Sites must have a core team with the expertise to deliver the TK-MT protocol: a primary investigator (PI) to lead the site-level team; a medical doctor (MD) to confirm clinical eligibility and provide medical oversight during the study; subject matter experts (SMEs) in culinary arts, nutrition education, exercise science, mindfulness training, and health coaching to facilitate class sessions; and research staff and infrastructure to conduct the clinical trial.

The TK-MT is being conducted at four U.S. academic institutions within the Teaching Kitchen Collaborative (TKC) [43] network; Dartmouth Health (DH), a rural academic medical center serving Northern New England; the University of Texas Health Science Center Houston (UTHealth Houston) School of Public Health, an urban, public university in the southwest United States, and two urban, public universities in the western United States—University of California, Irvine (UCI), and University of California, Los Angeles (UCLA). The Harvard T.H. Chan School of Public Health (HSPH) is serving as the coordinating center.

The coordinating center will oversee the conduct of the study, compliance with IRB regulatory matters, distribution of curriculum materials, maintenance of consistent data collection, and the conduct of regular primary investigator and study team meetings. HSPH will conduct power analysis, direct participant randomization, and provide overall data management and data analysis. Data will be securely stored in password-protected REDCap (14.5.25, Vanderbilt University, Nashville, TN, USA) databases maintained by each individual study site; de-identified data will be shared with the coordinating center for network-wide analyses.

### 2.3. Study Population

#### 2.3.1. Participant Eligibility

Sites will recruit adults aged 21–70 who are at increased metabolic risk based on a classification of overweight or obesity (BMI 25–39.9 kg/m^2^) and the existence of at least one metabolic abnormality (liver, blood glucose, or lipids) identified through baseline laboratory assessments (Table 1).

Participants must have reliable Internet access at home and two devices such as a smartphone, tablet, or computer that they are comfortable operating independently (at least one must have a camera) (smartphone, tablet, or computer). Hotspots can be provided to interested participants who do not have reliable Internet access. Participants must have minimal operating cooking equipment and utilities at home, including a cooktop, oven, refrigerator, electricity, and running water.

The exclusion criteria are as follows: individuals who currently take diabetes or weight loss medications (except for metformin); have a history or current diagnosis of Type 1 or 2 diabetes; history of weight loss surgery; severe food allergies; or plan to relocate within two years. Any individuals planning to participate in other longitudinal or intensive culinary medicine or weight management programs during the study period or have participated in the past. Any individuals with recent psychiatric hospitalizations, significant mental health diagnoses, recent life-threatening illnesses, alcohol or substance misuse issues, or limitations that would prevent safe participation in the program. Individuals who are imprisoned, unable to provide informed consent, or unable to participate in all study activities. And individuals who are currently or planning to become pregnant within 18 months.

#### 2.3.2. Sample Size Estimation

A proposed sample size of 320 participants (4 study sites × 2 cohorts × 20 participants per arm) will have 80% power to detect significant improvements in metabolic syndrome biomarkers ranging from 14.2 to 30.15%, assuming that control group participants have improvements ranging from 5 to 15% for ɑ = 0.05 by using a two-sample *t* test. Power analysis calculations for sample size are based on reported effect size estimates of metabolic syndrome markers (Appendix A) [44].

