## Appendix A

The target study population is 320 participants based on the capacity of a teaching kitchen (20 study participants in the TK arm and 20 in the control group times two cohorts at each of four sites). Power calculations using a total sample size of 320 participants indicate that the teaching kitchen intervention is designed to detect a significant improvement in metabolic syndrome biomarkers, with an improvement rate of approximately 31.8% needed in the intervention group to demonstrate a meaningful effect compared to the control group.

Improvement in at least one of the following metabolic markers (fasting plasma concentrations of glucose, insulin, ALT/AST, and lipids including cholesterol, triglycerides, LDL, HDL, and cholesterol HDL cholesterol ratio or the triglyceride HDL cholesterol ratio) after participation in our TK intervention.

Given that:

- There are two arms: control group and intervention group.
- Total sample size is 320.
- Two-sided test.
- Under a significance level of 0.05.

Assume that the percentage of improved study population in the control group is ranging between 5% and 15%.

**Table A1 nutrients-17-00314-t0A1:** Test: Two-Sample Proportional Test.

Assumed Prevalence in Control Group	Proportion Randomized to the Intervention Arm	Minimum Detectable RELATIVE Risk *		Percentage of Improved Study Population in Intervention Group	
		Power = 0.8	Power = 0.9	Power = 0.8	Power = 0.9
5%	0.3	2.95	3.39	14.75%	16.95%
	0.5	2.84	3.21	14.20%	16.05%
	0.7	3.14	3.52	15.70%	17.60%
10%	0.3	2.22	2.46	22.20%	24.60%
	0.5	2.14	2.35	21.40%	23.50%
	0.7	2.29	2.51	22.90%	25.10%
15%	0.3	1.92	2.09	28.80%	31.35%
	0.5	1.86	2.01	27.90%	30.15%
	0.7	1.96	2.12	29.40%	31.80%

Assumed prevalence is the percentage of improved study population; * the ratio of prevalence in the intervention arm over that in the control arm; calculations based on effect estimates as reported in Effectiveness of a Lifestyle Intervention on Metabolic Syndrome. A randomized controlled trial [44].

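### The 80% power range in section 2.3.2 takes its upper limit from the 90% column of Table A1 and names a different test, and Appendix A's unlabelled 31.8% belongs to a 70:30 allocation

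*Protocol article*

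**What the plan says.** Section 2.3.2 builds the sample size as "4 study sites × 2 cohorts × 20 participants per arm", which is 320 in total. It claims "80% power to detect significant improvements in metabolic syndrome biomarkers ranging from 14.2 to 30.15" percent, assuming control improvement of 5 to 15% and alpha 0.05. It names a two-sample t test and refers to Appendix A for the calculation.

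Appendix A uses the same total ("Power calculations using a total sample size of 320 participants") and the same equal split ("20 study participants in the TK arm and 20 in the control group times two cohorts at each of four sites"). Its stated conditions are "Two-sided test" and "Under a significance level of 0.05". Table A1 is headed "Test: Two-Sample Proportional Test", and its outcome is the percentage of the study population that improved. The table covers three control rates (5, 10, 15%), three proportions randomised to intervention (0.3, 0.5, 0.7) and two power levels (0.8, 0.9).

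The opening paragraph of Appendix A also summarises the result as a design "with an improvement rate of approximately 31.8% needed in the intervention group to demonstrate a meaningful effect compared to the control group". That sentence gives no power level, control rate or allocation.

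**The concern.** Section 2.3.2 attaches one power level, 80%, to a range whose two ends come from different power columns of Table A1. Read at face value, it tells the reader that 15% against 30.15% is the limit of what the trial can detect with 80% power. The table says that limit is lower.

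The test and the quantity also differ between the two places. A t test on improvements in biomarkers, expressed in percent, reads like a comparison of mean percentage change. The calculation behind it compares the proportions of participants who improved on at least one marker. Nobody reading section 2.3.2 alone would know that.

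The 31.8% in Appendix A is a further figure for the same trial. It matches neither the range in section 2.3.2 nor any 1:1 entry in the table. At stake is whether the power statement can be relied on as a description of the design. Patient numbers and conduct are not affected.

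**Working it through.** **Inputs.** Total 320; 20 per arm × 2 cohorts × 4 sites = 160 per arm (section 2.3.2, Appendix A). Two-sided alpha 0.05 (Appendix A). Control rates 5, 10, 15% (Table A1). The listed inputs include no dropout allowance, so all 320 are taken as analysed.

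**Formula.** Two-sample test of proportions, pooled variance under the null:

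power = Φ[(p2 − p1 − 1.96·s0) / s1], where
- s0 = √[p̄(1 − p̄)(1/n1 + 1/n2)], with p̄ the average rate weighted by arm size
- s1 = √[p1(1 − p1)/n1 + p2(1 − p2)/n2]

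**Step 1: reproduce Table A1.** Solving for the detectable intervention rate reproduces all 18 cells within 0.11 percentage points. The 1:1 rows:

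| Control | 80% power: table / recomputed | 90% power: table / recomputed |
|---|---|---|
| 5% | 14.20 / 14.19 | 16.05 / 16.05 |
| 10% | 21.40 / 21.35 | 23.50 / 23.44 |
| 15% | 27.90 / 27.80 | 30.15 / 30.04 |

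The table is sound. Its percentages are control rate × printed relative risk: 0.05 × 2.84 = 14.20%, 0.15 × 1.86 = 27.90%, 0.15 × 2.01 = 30.15%.

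**Step 2: test the range in section 2.3.2 at 160 per arm.**
- Lower end, 5% v 14.2%: s0 = 0.03294, s1 = 0.03253; (0.092 − 0.06456)/0.03253 = 0.844; power 0.80. Correct.
- Upper end, 15% v 30.15%: s0 = 0.04674, s1 = 0.04597; (0.1515 − 0.09161)/0.04597 = 1.303; power 0.90, not 0.80.
- Table's 80% entry, 15% v 27.9%: s0 = 0.04589, s1 = 0.04532; (0.129 − 0.08994)/0.04532 = 0.862; power 0.81.

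The stated upper limit is therefore 30.15 − 27.90 = 2.25 points above the table's own 80% value.

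**Step 3: could another method explain 30.15% at 80% power?** For 15% v 30.15% at 1:1, power is 0.878 with continuity correction, 0.909 with unpooled variance, 0.907 with the arcsine method, and 0.908 with a t test on 0/1 data. None is near 0.80. With continuity correction the 1:1 limit at 80% power is 28.5%, still short of 30.15%. Eighty percent power for that contrast needs 119 per arm (238 in total). Dropout would have to be (320 − 238)/320 = 26% to explain it, and no such allowance is stated.

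**Step 4: the 31.8%.** In Table A1 it occurs once: 15% control, 0.7 to intervention, power 0.9 (0.15 × 2.12 = 31.80%).
- At 70:30 (224 v 96): s0 = 0.05400, s1 = 0.04792; (0.168 − 0.10584)/0.04792 = 1.297; power 0.90. This agrees with its cell.
- At 1:1 (160 v 160): s0 = 0.04733, s1 = 0.04639; (0.168 − 0.09277)/0.04639 = 1.62; power 0.95.

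**Step 5: effect of the test label.** A t test on 0/1 data gives 0.805 for 5% v 14.2% and 0.810 for 15% v 27.9%, against 0.801 and 0.806 for the test of proportions. The wrong label barely moves the numbers; it misdescribes what was calculated.

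**The case against.** The case for treating this lightly is substantial, and most of it stands. The primary aim is feasibility, analysed descriptively, and the power statement concerns secondary, preliminary efficacy. Appendix A says the target of 320 follows from teaching-kitchen capacity, so no sample size was solved from the misquoted figure. The lower limit is right, Table A1 is right, and both text figures overstate the rate that must be reached. A reader might infer that the trial is underpowered for what it claims. The recomputation shows the opposite: about 90% power at 30.15% and about 95% at 31.8%.

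On 31.8%, it is fair to say that the sentence makes no 80% claim, so its distance from 27.9% should not be counted as an error in an 80% limit. It is also the largest value in Table A1 and could have been meant as a worst case over all scenarios. But the text does not say so, and the same paragraph describes 20 and 20 per cohort. What stands is that the figure is unlabelled and does not belong to the trial's allocation.

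A reader might also infer that the plan gives three competing required effects (27.9, 30.15 and 31.8%). It does not: only 31.8% is called needed, while 27.90% and 30.15% are correct 1:1 entries for different power levels. Nor are the 0.3 and 0.7 rows wrong; they are correctly computed and clearly labelled alternatives.

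None of this accounts for section 2.3.2 attaching 80% to a 90% entry, or for naming a test that its own source does not use.

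**Conclusion.** The statement is wrong as written, with moderate severity. With 320 participants at 1:1, the 80% power range for control rates of 5 to 15% is 14.2% to 27.9%, not 14.2% to 30.15%. The test in section 2.3.2 contradicts Table A1, and its wording invites a reading as mean biomarker change that the calculation does not support. The 31.8% in Appendix A is a 70:30, 90% power figure presented without those conditions for a 1:1 trial.

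The errors are conservative and change neither the sample size nor the design. The conclusion assumes 160 analysed per arm, independent participants, two-sided alpha 0.05 and the pooled test of proportions that reproduces the table. The mismatch between text and table does not depend on any of these, since it can be read directly from Table A1.

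**What to change.** In section 2.3.2, state that 320 participants (160 per arm, 1:1) give 80% power, by a two-sided two-sample test of proportions at alpha 0.05, to detect 14.2%, 21.4% and 27.9% of participants improved against 5%, 10% and 15% in control (90% power: 16.05%, 23.5% and 30.15%). Remove the reference to a t test, and say that the quantity is the proportion of participants who improved.

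In Appendix A, replace 31.8% with the matching 1:1 value for a 15% control rate (27.9% at 80% power or 30.15% at 90%), and state the power level and control rate beside it. The 0.3 and 0.7 rows of Table A1 may stay if marked as not the trial's allocation.

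The cost is a text correction. Sample size, conduct and analysis are unchanged.

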#### 2.3.3. Recruitment and Randomization

Potential participants will be recruited through the TK-MT website, paid social media advertisements, physical and digital flyers, social media postings, institutional emails, television spots, ads in community newspapers, booths at health fairs, and referrals from research or clinical staff at the study sites. Study recruitment will follow the process outlined in Figure 1. Preliminary study eligibility will be assessed through an optional pre-screening survey on the TK-MT website followed by a screening phone call.

Alternatively, interested individuals can call the study team directly and complete a phone call screening. Those who are likely eligible based on the phone call screening will complete a follow-up video call with a trained research assistant (RA). These screening methods will collect eligibility data and visually confirm minimal operating kitchen equipment described in the inclusion criteria. The RA will explain the study details and obtain informed consent during these screening calls. Final eligibility will be confirmed by study site PI based on a review of anthropometric data, laboratory data, self-reported medication lists, and study site MD recommendations.

Eligible participants will be randomized at the site level in blocks to either the TK-MT intervention group or the wait-list control group receiving standard care (i.e., followed as usual by their primary care physician). Each site will independently enroll 1–2 cohorts and randomize 28–48 participants to each study arm (for single-cohort sites) or 14–30 participants per arm (for double-cohort sites); the wait-list control group will receive a condensed version of the intervention curriculum after completing the 12-month assessments. Individuals who share a household can participate in this study only if they have separate kitchen workspaces for virtual classes and must be randomized to the same study arm. All recruitment and randomization data will be documented in site-specific REDCap surveys and forms. Incentives, in the form of gift cards and small gifts (notepad, measuring spoons, etc.) valued at a total of USD 200 per individual will be provided after completing (1) laboratory and anthropometric screening, (2) baseline psychometric assessments, (3) 4-month assessments, (4) 12-month assessments, and (5) 18-month assessments.

